# 7. SAFETY REPORTING

## 7.1 Section 10 WMO event

In accordance to section 10, subsection 1, of the WMO, the investigator will inform the subjects and the reviewing accredited METC if anything occurs, on the basis of which it appears that the disadvantages of participation may be significantly greater than was foreseen in the research proposal. The study will be suspended pending further review by the accredited METC, except insofar as suspension would jeopardise the subjects’ health. The investigator will take care that all subjects are kept informed.

## 7.2 Adverse and serious adverse events

Adverse events or adverse reactions are defined as any undesirable experience occurring to a subject during this randomised clinical trial. All adverse events reported spontaneously by the subject or observed by the investiga­tor or his staff will be recorded.

A serious adverse event (SAE) is any untoward medical occurrence or effect that at any dose results in death;

- is life threatening (at the time of the event);
- requires hospitalisation or prolongation of existing inpatients’ hospitalisation;
- results in persistent or significant disability or incapacity;

All serious adverse events will be reported to the accredited METC that approved the protocol, according to the requirements of that METC.

## 7.3 Follow-up of adverse events

All adverse events will be followed until they have abated, or until a stable situation has been reached. Depending on the event, follow up may require additional tests or medical procedures as indicated, and/or referral to the general physician or a medical specialist.

# 8. STATISTICAL ANALYSIS

Data will be analysed by the intention-to-treat principle. Demographic characteristics, variables from laboratory analysis and quantitative variables obtained from the clinical evaluation (Pain score, opioids consumption) will be reported as means, medians or percentages together with their standard deviations, as appropriate.

We will perform the following analysis of the primary endpoint. In all patients we test for a difference in mean pre- and post-operative extension angles between those with and without Cryoseal. Adjusting for pre-operative extension angles by analysis of covariance, we perform a two-sided test at level 0.049. In a secondary analysis, Fisher’s exact test will be used to determine the effect of use of fibrin sealant on adverse events. We will investigate whether the Cryoseal effect is modified by the use of a drain by adding drain use and the interaction between drain use and Cryoseal to the above analysis of covariance model. Also, effects within various other patients groups will be studied (e.g. gender, age, adipositas and rheumatic disorders)

Interim analysis and stopping rule:

We plan to perform a single interim analysis when a total of 250 patients have been included. At this time we will decide if the trial should be terminated early for efficacy. In all patients we test for a difference in mean pre- and post-operative extension angles between those with and without Cryoseal. Adjusting for pre-operative extension angles, we perform a two-sided test at level 0.005. If we are able to reject the null hypothesis, we terminate the trial and conclude efficacy of the treatment.

If the stopping rule is not met and the trial continues, we must set the level of significance of the final analysis to 0.049 to account for the fact that we performed an interim analysis. This is referred to as the O'Brien-Fleming rule.

Also, if the trial continues, we will use the available data to estimate the standard deviation of the primary outcome. Based on this estimate, we will re-compute the sample size that is needed to achieve 90% power to detect a 10 degree difference between the study arms at level 5%. We will adjust the sample size accordingly. However, we will not include less than 400 patients or more than 600 patients.

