# SUMMARY

**Rationale:** Fibrin Sealant is known to have some potential benefits for intraoperative use, especially in the acceleration of the coagulation cascade. Most studies with fibrin glue are focussing on the reduction of allogeneic blood transfusion and the possibilities to reduce costs. Firstly, fibrin sealant was made from patients’ blood plasma but the logistic problems made introduction in general hard. Now Sanquin has produced a CryoSeal (fibrin sealant) made of single-donor plasma which can be used during surgery. This application is already used in cardiothoracic surgery.

**Objective:** Is the application of CryoSeal (CS) in primary total knee replacement surgery beneficial for the patient with respect to a faster track and improved postoperative rehabilitation. The beneficial effect may be due to quicker functional knee rehabilitation, by pain reduction, better mobilisation and improved quality of life during the early postoperative period.

**Study design:** Multicenter, randomised controlled trial stratified by clinic.

**Study population:** Patients aged above 18 years scheduled for primary total knee replacement (TKA) because of osteoarthritis or rheumatic arthritis, meeting all the inclusion criteria and none of the exclusion criteria, are eligible for inclusion in the study.

**Intervention:** The intervention is the application of CryoSeal during surgery according to the standardised manner. The control group will receive standard care.

**Main study parameters/endpoints:** Primary endpoint: Difference in extension knee function 2 and 6 weeks after surgery. Secondary endpoints: postoperative complications, Pain score, knee function Flexion/Extension, Barthel score (day 3); Outpatient department scores (2 weeks, 6 weeks and 3 months, 1 year): Complications, Pain knee function, KSS, KOOS, SF-12, IPQ-K and EQ5D. A pre- and postoperative hand strength measurement will be performed since this might be a predictor of outcome after TKA. (Taekema 2010). Where possible, an actual physical activity measurement will take place to objectively analyse pre- and post operative acitivity level. (Groot, de 2008)

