# 3. STUDY DESIGN

The study is a randomised, multi centre trial in orthopaedic surgery in patients who receive a primary total knee replacement. Patients will be randomised in two groups. The intervention group will be treated with CryoSeal per operative and the control group will receive standard care (no additional treatment during surgery). Patients will be stratified prior to randomisation in six strata occording to the the clinical site where the use of postoperative wound drain is the standard procedure. No consensus between the sites exists on the usage of the latter.

Patients and observers will be blinded for treatment until 3 months postoperative.

See Flow chart next page

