## 6.2 Randomisation, blinding and treatment allocation

Patients are included after signing the Informed Consent form. Patients will be stratified per clinic. Randomisation is done by web based computer application. Each centre will have its own username and password with a specific randomisation in blocks with a variable amount of patients. Block randomisation is used to get an equal distribution of patients in each treatment group for the interim and final analysis. Per randomisation patients characteristics like gender and date of birth are asked to prevent scrambling.

Each centre should randomise at least 50 patients to receive an equal distribution over the participating centres. Patient and assessors are blinded for the intervention by the patient. After 3 months follow-up, the treatment arm is communicated with the patient.

All patients are followed according to the intention-to-treat principle. Patients will be registered using a patient number, date of birth and study number and all other data will be coded by linkage to the study number.

An analysis plan will be enclosed as an addendum of this protocol 4.1 and before the study will be de-blinded.

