1. Hospital stay in days
2. Years of age

Categorized variables

1. Hospital stay: <3; 3-5; 6-8; >8 days
2. Age: >70; 70-60; <60 years of age

The subgroup analyses above are explorative for hypotheses screening.

Extra secondary analyses: Observational analyses of the RCT dataset:

When no correlation between the use of CryoSeal and the pre-, peri- and postoperative variables can be demonstrated and the above estimates are homogenous over the study arms, they will be pooled over the strata before further subgroup analysis; univariate followed by subsequent multivariate analysis will be performed.

The following research questions will be investigated by post-hoc analyses:

Preoperative variables:

1. Is there a correlation between preoperative hand grip strength and postoperative complications after > 1 year?
2. Are there associations between pre-op outcomes of the questionnaires and post-op functional/QoL/complications?
3. Is there a correlation between Range of Motion (ROM) and Oxford Knee Score outcomes?
4. Is there a correlation between preoperative NSAID (incl. Asperin) use and primary and secondary outcomes?
5. Is there a correlation between preoperative Prednison use and primary and secondary outcomes?

Perioperative variables:

1. Is there difference in post-op outcomes between LPS cemented vs cementless (Haga vs Spaarne) knee protheses
2. Is there difference in post-op outcomes (incl. hospital stay, body temp. (if applicable)) or -complications (incl. transfusion reactions) in transfused and non-transfused patients, or patients transfused at different indications/-triggers, and using different type of transfusion products
3. Are there more transfusion reactions in women?
4. Is there a difference in primary and secondary outcome between surgery type (“onder bloedleegte” or not)
5. Is there a difference in mean hospital stay and EPO use (if applicable)
6. Is there a correlation between wound catheter (incl. autologous reinfusion, if applicable) use vs no use and postoperative complications (bleeding, body temp).
7. Is there a correlation between perioperative wound drain reinfusion vs no reinfusion (if applicable) and postoperative complications
8. Is there a correlation between surgery time and postoperative outcomes of the questionnaires
9. Blood losses associated with type of catheter used
10. Is there a correlation between perioperative transfusion trigger (anaemia), age and length of hospital stay

Postoperative variables:

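### Randomisation is stratified by clinic but the interim and final ANCOVA leave clinic out: the CryoSeal test is valid but conservative whenever clinics differ, and several drain, drain-type and cement comparisons cannot be separated from hospital

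*Combined protocol and SAP*

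**What the plan says.** The Summary describes a "Multicenter, randomised controlled trial stratified by clinic". Section 6.2 repeats that "Patients will be stratified per clinic" and adds that "Block randomisation is used to get an equal distribution of patients in each treatment group". Section 3 places patients "in six strata occording to the the clinical site where the use of postoperative wound drain is the standard procedure" and remarks of drains that "No consensus between the sites exists on the usage of the latter".

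Section 8 gives the final primary analysis: "Adjusting for pre-operative extension angles by analysis of covariance, we perform a two-sided test at level 0.049". The interim test, at 0.005 with 250 patients included, also adjusts only for pre-operative extension. Effect modification by drain is examined by "adding drain use and the interaction between drain use and Cryoseal to the above analysis of covariance model". If the trial continues, the SD of the primary outcome is re-estimated and the total is reset within 400 to 600 patients.

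The addendum (15 May 2013) keeps the primary analysis as in the protocol. Clinic is not among its listed subgroup or multivariate variables. Its one reference to pooling across strata is conditional, concerns the extra observational analyses, and does not define the strata as clinics. Among its post-hoc questions is "Is there difference in post-op outcomes between LPS cemented vs cementless (Haga vs Spaarne) knee protheses", and it notes that a single hospital, with 73 patients, uses the Bellovac drain.

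**The concern.** Blocking within clinic balances the arms inside each hospital, so differences between hospitals drop out of the true sampling error of the CryoSeal contrast. A model without clinic still counts those differences in its residual. The reported standard error is then larger than the true one, the confidence interval is too wide, and the test rejects less often than its nominal level. The design has already paid for that precision. An SD that ignores clinic would carry the same excess into the sample-size re-estimation.

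The second issue is attribution. If drain use follows hospital practice, a drain effect also reflects whatever else differs between hospitals, such as case mix, rehabilitation or assessors. Where a drain type belongs to one hospital, or cementing is compared as one hospital against another, the factor and the hospital are the same variable.

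**Working it through.** **Inputs.** Difference 10 degrees, SD 35 degrees, 250 per arm, two-sided 0.049, power 90% (section 4.4); interim at 250 patients in total, level 0.005 (section 8); six strata (section 3). *Assumptions:* 35 degrees is the residual SD in the plan's model, and clinics explain a share q of that variance. The documents give no q, so it is varied from 0 to 0.15.

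**The plan's own figure.** n per arm = 2(1.969 + 1.282)² × 35² / 10² = 258.8, so 259 against the stated 250. Power at 250 per arm is 89.0%, close to the stated 90%. This small shortfall is a separate matter, and the present point does not depend on it.

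**Primary test.** The reported standard error without clinic is S = 35√(2/250) = 3.130. The true one under blocking by clinic is s = S√(1−q). Then:

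- overstatement of the standard error = 1/√(1−q) − 1
- true type I error = 2[1 − Φ(1.969/√(1−q))]
- power without clinic = Φ(10/s − 1.969/√(1−q))
- power with clinic = Φ(10/s − 1.969)

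At q = 0.10: s = 2.970; 1/√0.90 = 1.054; type I error = 2[1 − Φ(2.075)] = 0.038; power without clinic = Φ(3.367 − 2.075) = 90.2%; power with clinic = Φ(3.367 − 1.969) = 91.9%.

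| q (assumed) | SE overstated | True type I error | Power without clinic | Power with clinic | Gain (points) |
|---|---|---|---|---|---|
| 0 | 0% | 0.049 | 89.0% | 89.0% | 0 |
| 0.01 | 0.5% | 0.048 | 89.1% | 89.3% | 0.2 |
| 0.05 | 2.6% | 0.043 | 89.6% | 90.5% | 0.9 |
| 0.10 | 5.4% | 0.038 | 90.2% | 91.9% | 1.7 |
| 0.15 | 8.5% | 0.033 | 90.8% | 93.3% | 2.5 |

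**Check by simulation** (six clinics of 84, blocks of 4, 5,000 runs per setting). At q = 0.10, type I error was 0.039 without clinic and 0.047 with it, and power was 90.9% and 92.4%. At q = 0.05, type I error was 0.047 and 0.051, and power 90.2% and 91.0%. With a simulation error of about 0.003 on the type I figures, this agrees with the table in direction and size.

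**In patients.** For the model without clinic to match the power with clinic, n per arm = 250[(3.194 + 1.969(1 − √(1−q)))/3.194]². At q = 0.10 this is 266.1, or about 32 more patients in total; at 0.05 and 0.15 it is about 16 and 49.

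**Interim** (125 per arm, level 0.005). Power goes from 28.7% to 31.2% at q = 0.05, and from 28.2% to 33.5% at q = 0.10.

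**Re-estimation.** The required n scales with the residual variance: 259(1−q) gives 246 per arm at q = 0.05 and 233 at q = 0.10 (both at level 0.049). All three totals (518, 492, 466) lie inside the 400 to 600 limits, so the choice of SD would change the target.

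**Drain as a hospital factor.** Suppose six equal clinics (500/6 = 83.3 patients each) and drain wholly fixed by clinic (assumptions). The variance of a naive drain-versus-no-drain comparison is understated by a factor of 1 + 82.3 × ICC: 1.82, 2.65 and 5.12 at ICC 0.01, 0.02 and 0.05. A nominal 5% test then has a true level of 2[1 − Φ(1.96/√factor)], about 15%, 23% and 39%. This applies to the drain main effect and not to its interaction with CryoSeal.

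**The case against.** The strongest reply is that the primary consequence is mild. The CryoSeal estimate is unbiased, and the error rate moves in the safe direction. The loss depends on a quantity that the documents do not give, and it vanishes if clinics do not differ once baseline extension is in the model. All of this stands; the omission is certain, its size is not.

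A reader might infer a larger power gain by setting 93.3% against the nominal 89.0%, or by taking 500(1/(1−q) − 1) = 26, 56 or 88 extra patients at q = 0.05, 0.10 or 0.15. That credits the model with precision that the blocks already deliver. The 89.0% is power with no clinic variance at all; the proper comparators are 89.6%, 90.2% and 90.8%.

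A reader might also infer that section 8's drain analysis is confounded by hospital. Its stated question is the interaction, which rests on randomised contrasts within clinics. What remains is narrower: if drain is fixed by clinic, modification by drain cannot be told from modification by hospital.

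Nor does the addendum ignore hospitals. It names them in the cement and Bellovac comparisons, labels its research questions post-hoc and calls its subgroup analyses exploratory. Those labels disclose the setting but do not remove the confounding. A clinic term does not remove it either: it would eliminate a hospital-against-hospital contrast altogether.

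**Conclusion.** The point holds in a limited form. Clinic is the stratification factor and is absent from the model at both looks. The cost is a conservative test and intervals that are somewhat too wide: at an assumed clinic share of 5% to 15%, between 0.9 and 2.5 points of power at the final analysis, and nothing if the share is zero. The documents do not support a claim that this omission biases the CryoSeal result or makes it anti-conservative.

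The drain main effect (where drain follows clinic practice), Bellovac, and cemented versus cementless cannot be separated from hospital, and the plan does not say so. This limits what may be concluded from secondary and post-hoc analyses; the primary result is unaffected. The change is worth making but is not essential to the trial's validity.

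**What to change.** - **Section 8, primary analysis.** Fit the ANCOVA with treatment, baseline extension and clinic (fixed, six levels) at interim and final, and use that model's residual SD in the sample-size re-estimation.
- **Section 8, drain interaction.** Keep clinic in the model and keep drain use as the protocol defines it. State that, where drain follows clinic practice, the drain main effect is aliased with clinic and the drain-by-CryoSeal interaction cannot be told apart from clinic-by-CryoSeal.
- **Addendum, aliased comparisons.** Report cemented versus cementless and Bellovac as hospital comparisons from which no device or technique effect is concluded, and say that a clinic term cannot separate them.
- **Addendum, other pooled observational models.** Include clinic wherever the factor varies within clinic.

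The cost is five degrees of freedom and a few sentences, with no new data. The change should be written into the plan before the study is de-blinded.

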## 4.4 Sample size calculation

We performed a sample size calculation for our primary outcome which is pre- to postoperative difference in knee extension angle at two weeks after surgery. We expect to find a difference between study arms of 10 degrees, which we also feel is clinically relevant. We have little prior data to base our calculations on, but we expect a standard deviation of 35 degrees in our primary outcome. We conclude that we need 250 patients in each arm to be able to detect the stated difference at significance level 4.9% with 90% power.

We have made a slight adjustment to the usual significance level of 5% because we plan to perform an interim analysis when a total of 250 patients have been included. At this time we will decide if the trial should be terminated early for efficacy or futility. If the trial continues, we will use the available data to estimate the standard deviation of the primary outcome. Based on this estimate, we will re-compute the sample size that is needed to achieve 90% power to detect a 10 degree difference between the study arms at level 5%. We will adjust the sample size accordingly. However, we will not include less than 400 patients or more than 600 patients.

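### Adverse events are compared only by a Fisher's exact test pooled over clinics, and no overall between-arm estimate with a confidence interval is specified for them

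*Combined protocol and SAP*

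**What the plan says.** - **Adverse-event analysis (protocol, Section 8).** One sentence, placed under secondary analysis, says that Fisher's exact test "will be used to determine the effect of use of fibrin sealant on adverse events". It gives no effect measure, interval, significance level, sidedness or unit (patients or events), and no role for clinic.
- **Randomisation (protocol, Sections 3 and 6.2).** "Patients will be stratified prior to randomisation in six strata", defined by clinical site; Section 6.2 repeats: "Patients will be stratified per clinic". On size it says: "Each centre should randomise at least 50 patients". On allocation: "Block randomisation is used to get an equal distribution of patients in each treatment group".
- **Endpoints and definitions (protocol, Sections 6 and 7.2).** Complications are a secondary endpoint. Adverse events are defined more broadly, as any undesirable experience during the trial.
- **Addendum of 15 May 2013.** It plans an odds ratio or relative risk for CryoSeal with a 95% interval in each subgroup, for primary and secondary endpoints. It also refers to an analysis of the total dataset, by intention to treat and as treated, but for that it points back to the protocol and names no effect measure.

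**The concern.** A test result alone does not show how large an excess of complications the data still allow. The Summary and Section 5.2 already state that no toxicity is expected from this donor-plasma product, so a non-significant p-value could easily be taken as confirmation.

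Two features of the test add to this. Fisher's test has a true error rate below its nominal level, and in a safety comparison that lowers the chance of detecting a real excess. The test also ignores the clinics within which patients are randomised. Clinic differences are plausible from the documents: Section 3 says the sites do not agree on drain use, and the addendum contrasts cemented and cementless prostheses between two hospitals. Neither document says how far complication rates differ.

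**Working it through.** **Inputs from the documents.** 250 patients per arm (Section 4.4), a permitted total of 400 to 600 (Sections 4.4 and 8), six clinics of at least 50 patients (Sections 3 and 6.2), and allocation taken as 1:1.

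**Assumptions.** The documents give no adverse-event rate, no level for this test and no planned size for each clinic. I take a two-sided 5% level, event rates from 1% to 40%, and clinic sizes of 25, 30, 35, 40, 50 and 70 per arm (sum 250).

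**Step 1. The plan's own power figure.** It concerns the primary endpoint only: "We expect to find a difference between study arms of 10 degrees" and "we expect a standard deviation of 35 degrees in our primary outcome". Power = Φ(10 / (35·√(2/250)) − 1.969) = 89.0% at two-sided 0.049, close to the stated 90%. (The formula for exactly 90% gives 259 per arm.) So 250 per arm is a fair working size. The plan has no power statement for adverse events.

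**Step 2. True size of Fisher's test.** For a events in one arm and b in the other, the two-sided p-value sums the hypergeometric probabilities, given a + b, of all tables no more likely than the one observed. Mid-p counts the tables exactly as likely as the observed one at half weight. True size at event rate p is the sum over all (a, b) of Bin(a; n, p)·Bin(b; n, p), restricted to tables with p-value ≤ 0.05. With n = 250:

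| Event rate (assumed) | Fisher | Mid-p |
|---|---|---|
| 2% | 2.1% | 3.9% |
| 5% | 3.2% | 4.8% |
| 10% | 3.6% | 4.9% |

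**Step 3. Power.** The same sum with different rates in the two arms, n = 250:

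| Rates compared | Fisher | Mid-p | Loss (points) |
|---|---|---|---|
| 1% v 3% | 23.9% | 32.6% | 8.7 |
| 2% v 6% | 56.2% | 63.9% | 7.7 |
| 5% v 10% | 51.2% | 57.2% | 6.0 |
| 10% v 20% | 86.3% | 88.5% | 2.2 |
| 20% v 30% | 70.1% | 73.4% | 3.3 |

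At the 400-patient minimum, 2% v 6% gives 44.0% against 52.8%, and 5% v 10% gives 40.6% against 47.2%.

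**Step 4. Cost of ignoring clinic.** I compare a pooled Pearson chi-square with the Cochran-Mantel-Haenszel (CMH) statistic, so that Fisher's discreteness does not enter. With n_k per arm, N_k = 2n_k and m_k events in clinic k, CMH = [Σ(a_k − m_k/2)]² / Σ[n_k²·m_k·(N_k − m_k) / (N_k²·(N_k − 1))]. Simulation used 20,000 runs and a common odds ratio of 2; Monte Carlo error is at most 1.96·√(0.25/20,000) = 0.7 points.

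| Control rates by clinic (assumed) | Fisher | Pooled Pearson | CMH | CMH − Pearson |
|---|---|---|---|---|
| all 10% | 71.2% | 75.4% | 75.4% | 0.0 |
| 5–20% | 77.9% | 80.9% | 81.7% | 0.8 |
| 2–40% | 79.5% | 82.7% | 86.7% | 4.0 |

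With no treatment effect, pooled Fisher rejected in 2.9% to 3.6% of runs in these three settings, so it stays below 5%.

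**Step 5. What an interval adds.** Suppose 12/250 control and 24/250 CryoSeal patients have an event. Fisher gives p = 0.056. The risk difference is 9.6% − 4.8% = 4.8 points, with SE √(0.096·0.904/250 + 0.048·0.952/250) = 2.30 points and a 95% CI of 4.8 ± 1.96·2.30 = 0.3 to 9.3 points (Wald, unstratified). The p-value alone would read as no significant effect. The interval shows a doubled observed rate and an excess of up to 9 points not excluded.

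**The case against.** The strongest reply has four parts.

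- **Fisher's test is a standard, valid choice for a secondary safety comparison.** This stands. A reader might infer that ignoring the randomisation strata makes the comparison invalid; Step 4 shows that it does not. The cost is a little power, and only the widest assumed spread of clinic rates brings it to 4 points.
- **The power loss is small where events are common.** This also stands. Section 7.2 defines adverse events broadly, so the proportion of patients with at least one could be high, and there the loss is 2 to 4 points. Where Fisher loses most, power is poor with any test (1% v 3%: 24% against 33%). A reader might conclude that the planned test hides harm; the main limit for rare events is a sample size set for knee extension. The event rates are assumptions, not rates the documents expect.
- **The addendum already plans odds ratios with 95% intervals.** This stands in part. It would be wrong to say that the plan has no between-arm intervals at all. But those intervals are tied to subgroups, they cover complications only as a secondary endpoint, and they do not set an overall estimate for all adverse events or adjust for clinic.
- **Naming a test does not mean that only a p-value will be reported.** True, and that a null result would be misread is a prediction. But nothing in the plan commits the analysts to an overall estimate.

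**Conclusion.** The point holds as a gap in specification. Adverse events are to be compared by a pooled Fisher's exact test only, and no overall estimate with interval is set for them. At 250 per arm, two-sided 5% and assumed event rates of 2% to 10%, the test's true size is 2.1% to 3.6%. It gives up about 6 to 8 points of power against mid-p for 2% v 6% and 5% v 10%, and 2 to 4 points for 10% v 20% and 20% v 30%. Ignoring clinic adds about 0 to 4 points. All of these rest on assumed event rates, clinic rates, clinic sizes and test level.

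The documents do not support calling the safety analysis invalid. The missing overall interval is the main defect; the choice of test and the clinic adjustment are improvements that come at little cost. This is a minor point, worth correcting because correction is easy.

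**What to change.** In Section 8, define the overall adverse-event analysis as follows, separately for adverse events, serious adverse events and complications:

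- Report the number and percentage of patients with at least one event in each arm.
- Give the clinic-stratified Mantel-Haenszel risk difference with 95% CI: Σw_k(a_k/n_1k − b_k/n_0k) / Σw_k, with w_k = n_1k·n_0k/N_k.
- Test with Cochran-Mantel-Haenszel, or a stratified mid-p test, and state the level and sidedness.
- Keep an exact method for very sparse events.

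The cost is a few sentences in the plan and standard software output, with no extra data, patients or design change. There is a downside: the large-sample stratified methods are less reliable with very few events, which is why an exact method is kept, and mid-p does not strictly guarantee the 5% level.

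### The interim level of 0.005 and final level of 0.049 are not a matching O'Brien-Fleming pair, and together they spend slightly more than 5%

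*Combined protocol and SAP*

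**What the plan says.** **Overall target.** Section 4.4 explains the final level of 4.9% as a correction for the interim look: "We have made a slight adjustment to the usual significance level of 5% because we plan to perform an interim analysis".

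**Interim test.** Section 8 plans one look when 250 patients have been included: "Adjusting for pre-operative extension angles, we perform a two-sided test at level 0.005". The consequence is: "If we are able to reject the null hypothesis, we terminate the trial and conclude efficacy of the treatment".

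**Final test.** Section 8 specifies "Adjusting for pre-operative extension angles by analysis of covariance, we perform a two-sided test at level 0.049", because "we must set the level of significance of the final analysis to 0.049 to account for the fact that we performed an interim analysis". It adds: "This is referred to as the O'Brien-Fleming rule".

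**Sample size.** Section 4.4 plans 250 per arm, 500 in all. After the interim the final number may be re-set anywhere from 400 to 600. Neither section lets the two significance levels change with it.

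**Purpose of the look.** Section 4.4 says "At this time we will decide if the trial should be terminated early for efficacy or futility". Section 8 names efficacy only, and no futility criterion appears anywhere.

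**Inclusion.** Section 6.2 says "Patients are included after signing the Informed Consent form". The primary outcome in section 6 is measured 2 and 6 weeks after surgery.

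The analysis plan of May 2013 does not revisit the interim rule.

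**The concern.** A two-look design keeps its overall error rate only if the two levels are computed together, for the point at which the first look falls. Here a final level of 0.049 looks too generous for an interim level of 0.005, and both are fixed although the final sample size is settled only after the look. The adjusted final level is the plan's only protection of the 5% rate for its primary claim. If it is set too high, a final p-value of roughly 0.048 to 0.049 would be declared significant without support.

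Three wording points affect the same rule. The look is triggered by inclusions, so the text does not fix how many patients then have an outcome. The efficacy conclusion follows a two-sided rejection with no stated direction. The two sections disagree on whether futility is a reason to stop.

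**Working it through.** **Inputs.** Interim level 0.005 two-sided and final level 0.049 two-sided (section 8); 250 patients at the look and a final N of 500, or 400 to 600 after re-estimation (sections 4.4 and 8); difference 10 degrees, SD 35 degrees, 250 per arm (section 4.4). Allocation is taken as equal, in line with the blocked randomisation in section 6.2.

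**Method.** Under the null hypothesis the interim and final statistics Z1 and Z2 are bivariate normal with correlation √t, where t is the information fraction at the look. Total error = 1 − P(|Z1| < c1 and |Z2| < c2), by numerical integration. The critical values are c1 = 2.807 for 0.005 and c2 = 1.969 for 0.049.

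**Step 1: can 0.049 be reproduced?** At t = 250/500 = 0.5, O'Brien-Fleming uses c2 = C and c1 = C/√t. Solving for a total of 5% gives C = 1.9774, so c1 = 1.9774 × √2 = 2.797. The two-sided levels are 0.0052 and 0.0480. An O'Brien-Fleming-type spending function applied to two-sided 5% gives 0.0056 and 0.0478. With the interim held at exactly 0.005, the final level that gives 5% is 0.0481. With the final level held at 0.049, the interim level would have to be 0.0030. The stated pair is not reproduced.

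**Step 2: total error of the stated pair, with 250 measured.**

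| Final N | t | Total error, 0.005 then 0.049 | Final level giving 5% with 0.005 at interim |
|---|---|---|---|
| 400 | 250/400 = 0.625 | 5.01% | 0.0489 |
| 500 | 250/500 = 0.500 | 5.09% | 0.0481 |
| 600 | 250/600 = 0.417 | 5.14% | 0.0476 |

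At N = 500, for example, the interim contributes 0.0050 and the final look a further 0.0459, total 0.0509.

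**Step 3: fewer than 250 measured at the look.** The documents give no figure for this. As an assumption, take 214 measured. Then t = 214/400 = 0.535, 214/500 = 0.428 or 214/600 = 0.357, and the total is 5.07%, 5.13% or 5.18%. Fewer measured patients means a lower t, a weaker correlation between the looks and a larger total.

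**Step 4: power cost of the correction.** The standardised difference at 250 per arm is 10 / (35 × √(2/250)) = 3.194. Treating the final test as a single test, power at 0.049 is Φ(3.194 − 1.969) = 88.99%. At 0.0481 the critical value is 1.9765 and power is Φ(3.194 − 1.9765) = 88.84%. The loss is 0.15 points.

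**The case against.** **The excess is trivial.** It is 0.01 to 0.14 percentage points with 250 measured, and the final level is about 0.001 from where it should be. That is the size of a rounding or table-reading slip. This stands as a statement of size, and it rules out the larger claim that the trial lacks meaningful error control. It does not make the threshold right: the plan states it to three decimals, gives it one purpose, and it misses that purpose at each N checked.

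**Where 0.049 came from.** A reader might infer that the authors combined halves of two different boundary methods. Section 8 mentions only O'Brien-Fleming and no spending function, so the origin of the figure is unknown.

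**Direction.** A reader might infer that a significant result favouring control would be reported as efficacy. Read literally, the sentence allows it. But section 8 introduces the look as a decision about efficacy, section 2 frames the objective as improved extension, and section 6 hypothesises benefit. Reading the sign of the estimate after a two-sided test is normal practice. This is a gap in wording, not evidence of a likely wrong conclusion.

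**Trigger.** A reader might infer that consented but unmeasured patients count towards the look. Section 6.2 says inclusion follows consent; it does not say that signing defines the data cut, and a comparison of post-operative angles needs measured patients. What stands is that the documents never say how many must be measured.

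**Futility.** Stopping for futility cannot raise the type I error; it can only lower it. The conflict between sections 4.4 and 8 therefore concerns what the look is for, not alpha.

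**Conclusion.** The point holds, and it is small. The levels 0.005 and 0.049 are not the O'Brien-Fleming pair that section 8 says they are. Their total two-sided error is 5.09% at the planned size and 5.01% to 5.14% across the permitted range with 250 measured. Under the illustrative assumption of 214 measured, the range is 5.07% to 5.18%. Because the levels are fixed while re-estimation can place the look at 42% to 63% of the information, no single final level suits every outcome of the re-estimation.

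The trigger, direction and futility points are secondary: real ambiguities, cheaply removed.

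The figures assume one primary test per look, normal test statistics, and a re-estimation driven only by the standard deviation. Section 6 lists both 2 and 6 weeks as primary; testing both would be a separate multiplicity question, not counted here.

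**What to change.** 1. Keep 0.005 at the interim. Replace the fixed 0.049 in sections 4.4 and 8 with a rule: the final two-sided level is solved from the realised information fraction so that the total is 5%. With 250 measured this gives 0.0489 at N = 400, 0.0481 at N = 500 and 0.0476 at N = 600. Keeping 0.049 and tightening the interim to 0.003 is not a safe substitute: it fits only a look at half the information, and N is re-set afterwards (the total is 5.03% at N = 600).
2. Run the interim once 250 patients have a measured 2-week extension angle.
3. State that efficacy is concluded only if the adjusted difference favours CryoSeal.
4. Reconcile section 4.4 with section 8 on futility: remove it from 4.4, or state it in both places as non-binding so that it does not enter the levels.

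**Cost.** Text changes in two sections, about 0.15 points of power at 250 per arm, and a somewhat later interim, since the last of the 250 must have had surgery and reached the 2-week visit.
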